### Process evaluation measures

The following evaluation measures will be reported on at follow-up.

Engagement: We will track access and use of the web programme by ECEC services using website analytics (eg, number of webinar views). The completion status of the action plan for each service will be monitored. We will also record the number of primary and secondary caregivers interacting with monthly e-newsletters (eg, open/click rate) and accessing embedded resource links (ie, Lumpy Road to Solids website and resources). Finally, we will report the number of text messages successfully delivered.Acceptability: Intervention ECEC managers and educators will be asked to report on the acceptability of the intervention using four items based on the validated Acceptability of Intervention Measure tool.^64^ Caregivers will be asked to assess the acceptability of the intervention components using measures developed by the research team.Feasibility: Feasibility will be assessed with ECEC services via a survey using four items (three questions on a Likert scale and one open-ended item) adapted from the Feasibility of Intervention measure.^64^Fidelity: Fidelity of HPO implementation strategies within ECEC services will be measured using monitoring instruments within REDCap.

### Other outcome data

#### Demographic data

##### ECEC characteristics

At baseline, we will collect days and hours of operation, service size (number of children), number of educators (including those in the infant room), number of children in infant room, number of culturally and linguistically diverse child enrolments, whether they provide all food on site, and whether they are receiving any other active interventions.

##### Caregiver and child demographic data

Sociodemographic variables collected at baseline will include primary caregiver’s year of birth, relationship to child, cultural background, employment type, timing of return to work following birth (where applicable), marital status, experience parenting (first time), education level, self-reported height and weight, perception of income stress, current pregnancy status, breastfeeding status, and whether they are receiving ongoing support around infant feeding. Primary caregivers will also be asked about their child’s height and weight, living arrangements and enrolment at other ECEC services.

At baseline and follow-up, the following variables will also be assessed, as they represent likely mechanisms through which the intervention may exert its effects, as outlined in figure 2.

### Primary caregiver–ECEC provider relationship

We will assess caregiver–educator partnerships using an adapted version of the Parent/Teacher Relationship Quality Scale.^65^ Primary caregivers (8 items) and educators (11 items) will each complete a separate version of this scale to assess trust in communication regarding children’s nutrition. Each item is rated on a 5-point Likert scale from strongly disagree to strongly agree. The responses to each item will be summed to provide an overall score.

### ECEC educator and caregiver self-efficacy

Educators will be asked to rate their confidence with delivering various responsive feeding practices. Responses will be rated on a 5-point Likert scale from ‘not at all confident’ to ‘extremely confident’. Similarly, primary caregivers will complete self-efficacy questions assessing their confidence in relation to child feeding practices. Questions are based on the Maternal Self-Efficacy scale.^66^

### Communication between ECECs and caregivers

ECEC managers will be asked about the following types of communication with caregivers using questions previously used by the research team. Questions will address:

The type of breastfeeding and infant feeding information provided to newly enrolled primary caregivers of infants.Availability of information regarding breastfeeding and infant feeding on the website.Education provided to families in the last 12 months regarding infant nutrition through workshops, webinars or meetings.Whether infant feeding information from a recognised health authority was shared with families in the last 12 months.Whether ECECs display posters, stickers or signage promoting healthy infant feeding and breastfeeding.

ECEC managers^1^ will also be asked if educators have access to resources to facilitate nutrition conversations with primary caregivers as needed. Educators will also be asked about the frequency with which they provide feeding and nutrition information to primary caregivers regarding their children (eg, types and amounts of foods consumed, new foods they have tried, progression of self-feeding skills) at baseline and follow-up.

### Data collection and trial management

Data will be handled in accordance with ethical guidance and accessible only to named researchers on the ethics application. All electronic data will be stored on password-protected files on secure servers at Deakin University. Intervention data (eg, ECEC recruitment and randomisation schedules) will also be securely stored at HNE, as they are responsible for intervention delivery in the region. Primary caregivers’ mobile numbers will be shared with the HNE Population Health HB4HNE Kids team to avoid duplicate messaging. Paper forms will be scanned, electronically stored on secure servers and then destroyed.

The advisory group, consisting of all chief and associate investigators from all partner organisations listed on the ethics application, will meet quarterly to discuss trial conduct and audit trial progress.

### Data and safety monitoring

We do not anticipate any serious adverse events as a unique consequence of participation in this study. In the unlikely event this occurs, it will be reported to the Human Research Ethics Committee. A Data Monitoring Committee is not required for this study, as the intervention is non-clinical, poses minimal risk and does not involve the administration of a drug or investigational product. No interim analyses are planned.

### Sample size calculation

The sample size calculation was based on the primary outcome, zBMI. Based on our previous study,^55^ the SD is approximately 1.0 and mean zBMI is approximately 0.41. To detect a clinically meaningful change in population zBMI of 0.26 (69) with 80% power (two-sided α=0.05, intracluster correlation coefficient=0.02), we will need to recruit 540 caregiver–child pairs (270 per group) from 60 ECEC services. As an intention-to-treat analysis will be undertaken as the main analysis (participants analysed according to allocation group), we will not account for attrition.

### Statistical analysis

The primary analyses will be undertaken using an intention-to-treat approach, using multiple imputation to account for missing data. For the primary outcome (continuous zBMI), between-group differences at follow-up will be assessed using hierarchical linear regression models. We will also dichotomise the data to assess overweight/obese (zBMI using WHO cut-offs)^67^ and compare this using a logistic regression. All models will be adjusted for ECEC service-level clustering through a random effect and controlled for baseline measures and ECEC service SES and any other identified baseline imbalances. To assess differences between groups for secondary outcomes, linear regression analyses will be conducted (for continuous outcomes). Models will be adjusted for ECEC service-level clustering and any stratified variables through a random effect and controlled for baseline measures and ECEC service SES. Similar analysis will be undertaken for child-level secondary outcomes. All model inference will be conducted within the Bayesian framework. Sceptical, mean-centred normal prior distributions will be specified for the treatment effect and other fixed-effect regression parameters. A half-Student-t distribution will be used to model the SDs of random effects and residuals. Posterior draws will be obtained using the No-U-Turn Sampler, as implemented in the brms package for R.^68^ The probability of a favourable treatment effect (ie, the posterior probability that the treatment effect is greater than zero) will be reported, along with 95% credible intervals for the treatment effect parameters.

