### Randomisation

Following collection of primary outcome data (child weight and length), ECEC services will be randomly assigned to the intervention or a usual care control group in a 1:1 ratio. Randomisation will be stratified by Aboriginal and Torres Strait Islander child enrolments (≥10%), to ensure equity of access and SES (dichotomised as high/low SES according to the SEIFA classification^39^ of the ECEC service postcode), given the association between SES and child zBMI.^42^ We will apply block randomisation (4 or 6) to ensure group allocation is approximately equal. Randomisation will be performed using R (V.4.3.2) and completed by an independent statistician following baseline data collection.

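### The primary models leave out one of the two randomisation stratifiers and let chance baseline imbalance choose further covariates

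*Protocol article*

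**What the plan says.** The Randomisation section allocates services 1:1 and uses two service-level stratifiers: "Randomisation will be stratified by Aboriginal and Torres Strait Islander child enrolments (≥10" per cent), and "SES (dichotomised as high/low SES according to the SEIFA classification" of the service postcode). It gives equity of access as the reason for the first, and an association with child zBMI as the reason for the second.

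The Statistical analysis section describes the hierarchical linear model for zBMI and the logistic model for overweight/obesity. It then gives their adjustment. Clustering comes first: "All models will be adjusted for ECEC service-level clustering through a random effect". The rest of that sentence lists the covariates, for which the models are to be "controlled for baseline measures and ECEC service SES and any other identified baseline imbalances". The section goes on to the secondary outcomes and gives a different list: "Models will be adjusted for ECEC service-level clustering and any stratified variables through a random effect", with control for baseline measures and service SES. That second list has no imbalance clause.

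**The concern.** There are two faults in what the protocol states about the primary models.

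First, a factor that constrained the allocation is absent from the analysis. Stratifying balances the arms on that factor. If the factor also predicts outcome, a model that ignores it leaves its variance in the error term and reports more uncertainty than the design produces. Under the stated rule, enrolment could enter the primary model only if it were found to be imbalanced, which stratified allocation makes unlikely.

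Second, the clause on other imbalances leaves the rest of the primary covariate set to the observed data. After randomisation such imbalance is chance, and its size says nothing about whether a variable predicts zBMI. The rule can admit variables that do not matter and pass over variables that do. The baseline demographic sections list many service, caregiver and child characteristics, so the choice is wide. The primary outcome ends up with a less firmly specified model than the secondary outcomes.

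**Working it through.** **Comparison of the two covariate lists**

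| Element | Primary models | Secondary models |
|---|---|---|
| Service random effect | yes | yes |
| Baseline measures | yes | yes |
| SES stratifier | yes | yes, apparently twice (as a stratified variable by random effect, and as a control) |
| Enrolment stratifier | not named | yes, as a stratified variable |
| Covariates picked by imbalance | yes | not stated |

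**Reproducing the plan's sample size.** Inputs from the Sample size calculation section: SD 1.0, difference 0.26, two-sided α 0.05, power 80%, ICC 0.02, 270 per group, 60 services, hence 540/60 = 9 per service.

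- Individually randomised: 233 per arm.
- Design effect: 1 + (9 − 1) × 0.02 = 1.16.
- 233 × 1.16 = 270.3 per arm, against 270 stated.
- SE of the difference: √(2 × 1.16/270) = 0.0927. Power: Φ(0.26/0.0927 − 1.96) = Φ(0.845) = 80.1%.

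The planned size reproduces and is not in dispute.

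**What adding enrolment could gain.** With total variance 1, the between-service variance is 0.02 and the within-service variance 0.98. The variance of the difference is 2 × (9 × between + within)/270, which returns the 1.16 above: 9 × 0.02 + 0.98. Assume that enrolment alone explains a quarter of the between-service variance, 0.005:

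- 9 × 0.015 + 0.98 = 1.115.
- SE ratio: √(1.115/1.16) = 0.980, a fall of about 2%.
- SE: √(2 × 1.115/270) = 0.0909. Power: Φ(0.26/0.0909 − 1.96) = Φ(0.901) = 82%.

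The quarter is an assumption; the documents give no figure. Like the plan's own calculation, this takes no credit for baseline zBMI.

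**Does omission inflate error?** This was checked by simulation (20,000 replicates): 60 services of 9 children, allocation stratified on a binary service factor, ICC 0.02 and a t-test on service means. The share of services in the stratum (30%) and the stratum differences are assumptions.

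| Stratum difference in zBMI | Type I error, stratifier omitted | Type I error, stratifier included |
|---|---|---|
| 0 | 0.053 | 0.053 |
| 0.1 | 0.046 | 0.049 |
| 0.2 | 0.043 | 0.050 |
| 0.3 | 0.035 | 0.050 |

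The plan's ICC caps the plausible difference. A two-level factor with 30% prevalence contributes 0.3 × 0.7 × d² = 0.21d², so d cannot exceed √(0.02/0.21) = 0.31 even if it accounts for all between-service variance. The 0.3 row is at that ceiling. The simulation also adds the stratum effect on top of the 0.02, so it somewhat overstates the effect. It is a frequentist stand-in for the planned Bayesian model and includes neither SES nor baseline zBMI. Its message is about direction: omission is conservative.

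**The case against.** The strongest reply is that this is loose drafting with little consequence. The first adjustment sentence speaks of all models and the second, on stratified variables, follows closely, so the authors plainly meant to respect the stratification somewhere. The more natural reading still attaches the second sentence to the secondary outcomes it follows. Reading both as universal would only put two different lists on the same models. The section needs reconciling either way.

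On the imbalance clause, several safeguards are fair to mention. Baseline measurement precedes randomisation, the statistician is blinded to allocation, nothing makes covariate choice depend on outcomes, and sceptical priors on the fixed effects shrink weak covariates. These limit steering and harm. They do not supply a rule for what counts as an imbalance or make imbalance a guide to prognosis. A full analysis plan may list candidates, but the protocol already commits to selection by imbalance, so this is a rule fixed badly and not a detail left for later.

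It may also be said that fixed effects are a preference, since the secondary models use a random effect for stratifiers. That is partly so. But each stratifier has only two levels, so a random-effect SD would rest largely on its prior.

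Two stronger readings are tempting. A reader might infer that omitting a stratifier threatens the type I error; the check above shows the opposite direction. A reader might also credit the stratifiers with removing all between-service variance: 0.98 in place of 1.16 gives an SE ratio of √(0.98/1.16) = 0.919 and power of Φ(0.26/0.0852 − 1.96) = 86%. That is a ceiling for both factors together, and SES and baseline zBMI are already in the model. Nothing in the protocol shows that enrolment predicts zBMI; its stated purpose is equity.

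**Conclusion.** The point holds in a moderate form. The primary covariate list omits a design stratifier that the secondary list includes, and it admits covariates on the strength of chance imbalance. The omission costs some precision at most. The gain from correcting it lies between nothing and what enrolment explains beyond SES and baseline zBMI: about 2% of the SE and two points of power under the quarter-of-ICC assumption, and less if enrolment is weakly prognostic. The imbalance clause is the more serious half because it leaves the primary model open, although its effect cannot be given a size or a direction. The sample size stands.

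**What to change.** Specify the primary model as follow-up zBMI on arm, baseline zBMI, SES stratum and enrolment stratum as fixed effects, with a service random intercept. Use the same stratifiers in the overweight/obesity model.

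Align the secondary-outcome sentence with this, so that each stratifier enters once and in the same way throughout. Delete the clause on other baseline imbalances, or move it to a sensitivity analysis labelled as such. If further covariates are wanted in the primary model, name them in advance for their expected prognostic value.

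The cost is wording only: both stratifiers are known for every service at randomisation, and no new data are needed. The change should be made before follow-up outcomes are analysed.

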Infant feeding practices include the types and quantities of foods offered, the time and settings in which foods are offered, and primary caregivers’ feeding styles during mealtimes in the first 12 months of life.^13^ To help guide caregivers, Australia’s National Health and Medical Research Council (NHMRC) and the Australasian Society of Clinical Immunology and Allergy have published infant feeding guidelines (in 2012)^14^ and allergy prevention guidelines (in 2020)^15^ that include evidence-based recommendations for infant feeding. For infants <12 months, these include guidance around breastfeeding duration, and when and how to introduce solid foods, including allergy-causing foods.^14 15^ For toddlers 12–24 months, guidance includes recommendations for dietary patterns including no discretionary foods (ie, cakes, pastries, processed meat and sugar-sweetened beverages).^14 16^ Due to their high nutrient needs,^17^ there is no allowance for these foods in the diets of children under 2 years, as these foods are higher in saturated fat, added sugars and salt^16^ and may displace core food consumption.^18^,^20^ From 2 years onwards, the dietary guidelines provide specific recommendations for servings of core foods, including an allowance for discretionary foods, for each population group to meet nutritional needs.^16^

However, research suggests that implementation of infant feeding recommendations during this critical period is inconsistent.^18 21^ Encouragingly, the 2021 Australian Feeding Infants and Toddlers Study reported high breastfeeding rates with 98% of caregivers initiating breastfeeding from birth and over 40% continuing to breastfeed into the second year of life.^22^ In contrast, consumption of some core food groups was low, with two-thirds of toddlers aged 12–24 months not consuming the recommended daily serves for vegetables, and meats and alternatives.^18^ Moreover, 90% of toddlers consumed discretionary foods (sweet and savoury snacks) accounting for >10% of daily energy intake.^18^ A New Zealand study with 625 infants aged 7–10 months reported similar findings, where only 30%–60% of infants consumed vegetables, fruit and meat/protein-rich foods daily.^21^

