### Objectives

This cluster RCT aims to assess the efficacy of ‘Tiny Bites’, an 18-month digital health intervention delivered to ECEC educators and primary caregivers of children aged 4 to ≤12 months, relative to a usual care control group on child zBMI scores (primary outcome). We also sought to assess the impact of the ‘Tiny Bites’ programme at 18-month follow-up on:

Duration child receives any breastmilk.Child consumption of fruits and vegetables, ‘discretionary’ foods and consumption of any sugar sweetened beverages.Primary caregivers’ implementation of recommended infant feeding practices (as outlined in the Australian Infant Feeding Guidelines) and evidence-based responsive feeding behaviours.ECEC implementation of comprehensive nutrition and breastfeeding policies and adoption of evidence-based feeding recommendations including responsive feeding.Costs associated with intervention development, delivery and implementation.Cost-effectiveness of the intervention, expressed as the additional cost per 0.1 zBMI reduction.Potential adverse effects of the intervention (eg, food wastage, caregiver/ECEC staff complaints).Process evaluation measures including intervention engagement and acceptability (as reported by ECEC services and caregivers), and feasibility and fidelity (from the perspective of ECEC services).

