#### Secondary outcomes

The following will be assessed at baseline and 18-month follow-up.

Primary caregiver outcomes

Duration of any breast milk. Caregivers will be asked about current and past breastfeeding to determine duration of breastfeeding (completed months) and exclusive breastfeeding to 6 months if applicable.Child variety and frequency of fruit and vegetable intake (daily) Intake (at home) will be assessed using items from a Food Frequency Questionnaire^57^ and the Children’s Dietary Questionnaire, which has been validated in children aged 2–5 years old.^58^ The variety, frequency and quantity of fruit and vegetables consumed by the child will be captured, and an overall score for variety and frequency will be calculated.Child frequency of consuming discretionary food and sugar-sweetened beverage intake (daily, weekly or monthly). Intake (at home) will be measured using eight items from the validated Food Frequency Questionnaire.^57^ This will capture the frequency of discretionary food consumption, specifically processed meats, biscuits, fried foods and sugar-sweetened beverages.Caregiver adherence to infant feeding recommendations and responsive feeding practices. Questions on infant feeding practices, developed by the research team, will assess the timing of introduction to solid foods and drinking from a cup, and general feeding style. Responsive feeding practices will be evaluated using an adapted version of the validated Feeding Practices and Structure Questionnaire.^59^ We will assess how often caregivers appropriately respond to hunger and satiety cues, engage in persuasive feeding or use food as a reward.^59^ Items will be measured on a 5-point Likert scale from never to always. The responses to each item will be summed to provide a score for each construct.

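### Months of any breastmilk falls under linear regression, although some durations are fixed before randomisation and others are still running at follow-up

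*Protocol article*

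**What the plan says.** The Objectives section puts this outcome first among the secondary aims: "Duration child receives any breastmilk". Intervention design names longer breastfeeding as one of the programme's targets. Under Secondary outcomes the measurement is: "Caregivers will be asked about current and past breastfeeding to determine duration of breastfeeding (completed months) and exclusive breastfeeding to 6 months if applicable". The main quantity is therefore a number of months, asked about at baseline and at 18-month follow-up.

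Under Statistical analysis, for secondary outcomes, "linear regression analyses will be conducted (for continuous outcomes"). The models are adjusted for service clustering "through a random effect and controlled for baseline measures and ECEC service SES", and the section adds: "Similar analysis will be undertaken for child-level secondary outcomes". It names no time-to-event model, no at-risk analysis set and no rule for a child still breastfed at follow-up.

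Eligibility criteria sets the age at recruitment at 4 to 12 months, and Randomisation places allocation after baseline data collection. On background rates, the Introduction reports 98% initiation and "over 40% continuing to breastfeed into the second year of life".

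**The concern.** Three features of the outcome do not suit the stated model.

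1. **Fixed values.** A child weaned before baseline has the same duration at follow-up as at baseline. Nothing done after allocation can alter it.
2. **Lower bounds.** A child still breastfed at follow-up, aged about 22 to 30 months (4 + 18 to 12 + 18), has a duration that is still running. Linear regression takes the months so far as the final value. If the intervention works, more intervention than control children are cut off in this way.
3. **An ambiguous covariate.** A baseline duration of 5 months may belong to a child weaned at 5 months or to a 5-month-old who is still feeding. The first cannot change and the second can change a great deal. Baseline duration alone does not separate them.

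At stake is a named target of the programme: a real extension of breastfeeding could be reported as no clear effect.

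**Working it through.** **The protocol's own figure.** No sample size or power is given for breastmilk duration. The stated size for zBMI reproduces: 2 × (1.96 + 0.8416)² / 0.26² gives 233 per arm; design effect 1 + (9 − 1) × 0.02 = 1.16; 271 per arm, 542 in total, against 540 stated. This does not bear on the present point but supplies the 540 children used below.

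**Inputs.** From the protocol: 98% initiation and 40% at 12 months (Introduction; the text says over 40%, so this is a lower bound), age 4 to 12 months at enrolment, 18 months of follow-up, 540 children, 1:1 allocation. Assumed: constant weaning hazard, uniform enrolment age, hazard ratio 0.7 for stopping after enrolment, no clustering, a 5% two-sided test.

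**Step 1, weaned before enrolment.** Hazard h = ln(0.98/0.40)/12 = 0.0747 per month. Share still breastfed at enrolment = mean of 0.98·exp(−h·a) for a from 4 to 12 = 0.98 × [exp(−4h) − exp(−12h)]/(8h) = 0.547. So about 45% are already fixed.

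**Step 2, still breastfed at follow-up.** Control: 0.547 × exp(−18h) = 0.547 × 0.261 = 0.143. Intervention: 0.547 × exp(−0.7 × 18h) = 0.547 × 0.390 = 0.214. So 14% and 21% are censored.

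**Step 3, difference in observed months.** Mean further months within an 18-month window, for a child still breastfed at enrolment, is (1 − exp(−18k))/k.
- Control, k = 0.0747: 9.90 months.
- Intervention, k = 0.7 × 0.0747 = 0.0523: 11.66 months.
- Difference in children at risk: 1.76 months.
- Difference in all children: 0.547 × 1.76 = 0.97 months.

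**Step 4, power by simulation (at least 1,500 trials per setting).**

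| Hazard ratio | Linear, all children, baseline duration only | Linear, all children, baseline duration and status | Event rate, children at risk |
|---|---|---|---|
| 0.6 | 70% | 91% | 94% |
| 0.7 | 42% | 66% | 71% |
| 0.8 | 20% | 32% | 36% |

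Linear regression restricted to children at risk also gives about 66% at hazard ratio 0.7. With no true effect, the linear models show no bias and no inflation of the rejection rate.

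**Step 5, other duration shapes.** With 40% or 45% breastfed at 12 months, Weibull shape 1.0 or 1.3, follow-up of 18 or 21 months and hazard ratio 0.8:
- 41–45% are fixed at randomisation.
- 6–18% of control and 10–23% of intervention children are censored.
- The difference is 0.62–0.79 months in all children and 1.08–1.37 months in those at risk.

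**The case against.** The strongest reply concerns the source of the lost power. Baseline breastfeeding status is collected (Caregiver and child demographic data), and the wording on baseline measures does not exclude it as a covariate. Adding it to a linear model in all children raises power from 42% to 66% at hazard ratio 0.7, which is (66 − 42)/(71 − 42) = 83% of the gap to the event-rate analysis. This stands: most of the loss comes from not separating weaned from feeding children, and only a few points come from the linear form.

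Second, the average over all enrolled children is a legitimate intention-to-treat quantity, and months observed up to follow-up is a valid restricted-mean contrast if labelled as such. This also stands. The protocol, however, calls the outcome duration, with no such label.

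Third, an analysis plan that is not shown could define the analysis set or the censoring rule. It could, but the article does more than stay silent: it states a model for continuous secondary outcomes, and that model does not suit this one.

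Two stronger readings are tempting and are not supported.
- A reader might infer that exclusive breastfeeding to 6 months and the timing of solids also go into a linear model in all children. The first is naturally yes/no and is qualified in "to determine duration of breastfeeding (completed months) and exclusive breastfeeding to 6 months if applicable", while linear regression is confined to continuous outcomes. For the second, the questionnaire "will assess the timing of introduction to solid foods and drinking from a cup", but neither scale nor model is given.
- A reader might compare the planned estimate with the difference in complete, uncensored durations. That comparison depends on extrapolating weaning well beyond follow-up and does not measure error in anything the trial can observe.

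**Conclusion.** The point holds for duration of any breastmilk only. As written, the analysis mixes values settled before allocation, completed durations and lower bounds, and baseline duration alone cannot sort them. The consequence is an effect diluted by the share already weaned, cut further by the end of follow-up, and estimated with less precision than the data allow. Values fixed before randomisation are balanced in expectation, so there is no false-positive risk.

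The sizes are illustrations. Enrolment ages, the weaning curve and the hazard ratio are assumptions. Clustering is left out. The protocol plans Bayesian inference with sceptical priors, so power of a 5% test is only a proxy. The direction does not depend on the constant hazard, since the Weibull variants show the same pattern.

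**What to change.** In Statistical analysis, give this outcome its own model.

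- **Main analysis:** time to stopping any breastmilk among children still receiving it at baseline, using a discrete-time or Cox model with a service random effect, age as the time scale, entry at enrolment age, and censoring at follow-up for children who continue. The subset is defined by baseline status, before allocation, so the randomised comparison is preserved.
- **Secondary analysis:** months in the whole sample, adjusted for baseline breastfeeding status as well as baseline duration, and labelled as months observed to follow-up.

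The cost is small: a change of text and model code, with data already being collected. The downside is that the main estimate then applies only to children still breastfed at enrolment, which is why the whole-sample result should be kept beside it.
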